#### Status and timeline

Data collection began on June 28, 2024, with the first participant commencing the study on July 11, 2024. Data collection will continue until reaching the target sample size, which is estimated to be July 2026. Data will be available after the publication associated with those data.

#### Randomization

During the lab session (day 0), participants are randomly assigned to one of the two groups: an experimental (nap) group and a control (wake) group. All participants are mildly sleep deprived the morning of the lab session to increase the probability individuals in the nap group can both sleep and experience REM sleep. Participants are blinded to group allocation until immediately prior to the nap/wake period. Researchers are blinded to participant group allocation until after polysomnography set-up is complete. Thus, the polysomnography set-up for the wake group serves as a sham and to allow verification of sustained wakefulness during the experimental period. Groups of six participants are block randomized in equal numbers to each group and film order (out of two films), stratified by sex, to increase the likelihood of equal assignment over time. A researcher not involved in the administration of lab sessions ([name]) created a spreadsheet of participant allocation to group and film order using https://www.sealedenvelope.com/simple-randomiser/v1/lists. Cell blackout is used to conceal allocation until the researcher responsible for project administration ([name]) has completed polysomnography set-up.

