### Aims and hypotheses

The overall objective of this project is to examine two mechanisms underlying the relationship between sleep and the development of involuntary intrusive memories, utilizing a well-established experimental analog trauma exposure. The two mechanisms are:

Improved memory consolidation over periods of sleep leads to integration of the trauma memory into the broader memory network, thereby reducing intrusive memories.Sufficient sleep quality/quantity facilitates executive control over spontaneous cognition, including intrusive memories, decreasing the likelihood of their occurrence.

This study will employ a between-subjects design, with two conditions: (1) 2-h daytime nap opportunity, measured using polysomnography; and (2) equal length of controlled waking. Each condition will include *n* = 57 healthy adults, aged 18–49 years old (total *N* = 114, aiming for equal numbers of women and men). OSF preregistration: https://doi.org/10.17605/OSF.IO/MWAHD

Aim 1: Examine the effect of a daytime nap (vs. wake) on intrusive memory frequency.
Hypothesis 1.We will replicate the established finding that a nap, relative to wake, will result in a reduced number of intrusive memories [14, 15] in the 5 days following viewing the trauma film.

Aim 2: Investigate the effect of sleep-related memory consolidation on intrusive memory frequency.
Hypothesis 2a.A nap, relative to wake, will lead to greater recognition memory for the trauma film stimuli immediately after the nap/wake period, as measured by improved recognition of trauma stimuli from the film and reduced endorsement of lure stimuli (film images never seen).
 Hypothesis 2b.Recognition memory for the trauma film immediately after the nap/wake period will mediate the relationship between sleep condition (nap vs wake) and the number of intrusive memories in the following 5 days.

Aim 3: Investigate the effect of overnight sleep on mind wandering and intrusive memory frequency over a 5-day period following analog trauma exposure.
Hypothesis 3a.Reduced quantity of sleep at night will be associated with increased mind wandering and greater frequency of intrusive memories the next day.
 Hypothesis 3b.Mind wandering will mediate the relationship between sleep the previous night and intrusive memories the following day.

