### Participants and recruitment

#### Sample size

Our target sample size is 114 participants, with 57 in each condition. This study is powered primarily on Hypothesis 1, the group effect (nap vs. wake) on intrusive memory frequency. Relevant effect sizes were derived from a variety of prior studies, which have also been reported within at least one of four meta-analyses. Previous studies [14, 15, 25] examining the effect of a nap compared to wake on intrusion frequency have detected small to medium effect sizes (Hedges’ *g* = 0.38 [26] and 0.69 [15]) for between-group differences in intrusive memory frequency in the days following the experimental manipulation. Gvozdanovic et al. (2023) [14] also found a nap led to significantly fewer intrusive memories than the wake group, however, an effect size was not provided. For studies examining recognition memory for the trauma film following overnight sleep compared to wake or partial sleep deprivation [13, 23, 40], we calculated a sample size weighted average for Cohen’s *d*, finding a medium effect size of 0.5 for between-group differences where sleep, relative to wake, led to improved recognition memory for the film. Consistent with these studies, to detect a medium effect size of 0.5, with a two-tailed α of 0.05 and 80 per cent power, 57 participants are needed per group (114 participants in total) [41].

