##### Trauma film paradigm

The trauma film paradigm is used in this study to elicit intrusive memories [17]. Clips from two films are viewed in a small, sound attenuated room, and presented on a 24-inch screen with over-ear headphones for audio. Participants first complete a questionnaire about their current emotional state. They watch the trauma film (~12 min in total), which includes two scenes, one from the film Irréversible [57] and the other from a UK public safety advertisement on the dangers of texting and driving [58]. Both film scenes are fictional and have been used in previous studies [56, 59–63]. Film order is counter-balanced. Whilst participants view the films, we ask they maintain their concentration and continuously look at the scene. Upon completion, they rate their current level of distress and degree to which they were able to pay attention to the films. A camera in the room is used to monitor participants’ attention to the film. Participants are told prior to participating in the study they may watch positive, neutral or negative scenes, and are informed about the contents of the negative scenes prior to watching.

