#### Sleep schedule adherence

The sleep schedule is set in collaboration with the participant based on self-reported habitual sleep schedule. Each night and morning of the study, participants call the study phone and leave a message to indicate sleep and wake times. Sleep diaries and participant phone calls are monitored daily by the researchers. Within the first three nights of participation, if it is clear that the participant’s sleep schedule is different than what was initially set, the sleep schedule is adjusted to match the participant’s actual sleep schedule, as long as it stills falls within the study criteria (they do not sleep before 22:00 or after 01:00 and do not wake before 06:00 or after 09:00). If the sleep schedule is adjusted, participant wake time on the day of the lab session is also adjusted (to 2 h prior to regular wake time), as is lab session timing. Based on sleep diaries and sleep/wake time phone calls, participants are excluded from the study if they do not adhere to the sleep schedule for at least five nights. Non-adherence includes napping, going to sleep too early, or oversleeping. Participants are also excluded from the study if they wake 30 min after their scheduled wake time on the day of the lab session. If a participant is non-adherent to the sleep schedule, participation is rescheduled if there is agreement that they will be able to adhere for the rescheduled week. After the lab session, the sleep schedule is followed for one more evening. If participants are non-adherent to the sleep schedule on this evening (eg, napping following the lab session), they are excluded from the study and cannot be rescheduled.

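### A single published block length of six within sex makes up to a quarter of group allocations predictable before set-up is complete, and cannot balance film order within the nap and wake groups.

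*Protocol article*

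**What the plan says.** The Randomization section of the protocol article describes the scheme in one sentence: "Groups of six participants are block randomized in equal numbers to each group and film order (out of two films), stratified by sex". It mentions no second block length. The list was made by someone outside the sessions ("A researcher not involved in the administration of lab sessions"). Cells are blacked out until the researcher who administers the project has finished the polysomnography set-up, and the section states the blinding accordingly: "Researchers are blinded to participant group allocation until after polysomnography set-up is complete". The Trauma film paradigm section adds "Film order is counter-balanced", without saying whether that holds within each group.

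The Sleep schedule adherence section covers the week before allocation. The researchers check diaries and calls daily, may adjust the schedule in the first three nights, and exclude for non-adherence. After non-adherence, "participation is rescheduled if there is agreement that they will be able to adhere for the rescheduled week".

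On size, the protocol states "Our target sample size is 114 participants, with 57 in each condition", "aiming for equal numbers of women and men". Status and timeline gives July 2026 as the estimated end of data collection.

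**The concern.** Concealment has to cover the next allocation, and that includes what earlier allocations reveal about it. With one fixed block length, the last places in a block follow from the places already filled. Whoever sees each row as it is uncovered can work them out by counting. If people who can count in this way also help to decide whether a participant's schedule is adjusted or the participation rescheduled, then who takes a predictable place could come to depend on the expected group. Concealment exists to close that route to selection bias.

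A smaller matter is film order. Two groups and two orders make four cells. A reader may take the sentence on blocks to promise equal numbers in all four, which six places cannot give.

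**Working it through.** **Inputs.** Block length 6, two groups, two film orders, stratified by sex (Randomization); 114 participants, 57 per group (Sample size); equal sexes aimed for, so about 57 per sex (Aims and hypotheses). The protocol gives no figure for predictability, so there is none to reproduce. The scheme implies 114/6 = 19 blocks, or 57/6 = 9.5 per sex.

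**1. Allocations that could be known with certainty.** A block with 3 nap and 3 wake has C(6,3) = 20 equally likely sequences. An allocation is certain once one group's three places are used.
- Places 1 to 3: probability 0.
- Place 4: the first three are all one group, 2/20 = 0.10.
- Place 5: one group is used up in the first four, 2 × C(4,3)/20 = 8/20 = 0.40.
- Place 6: 1.00.

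The sum is 1.5 per block, and 1.5/6 = 25%. The general form 2m/(m+1) for blocks of 2m gives 6/4 = 1.5 at m = 3. Over 19 complete blocks this is 28.5 of 114. If each sex stops at 57 (nine full blocks and three places), it is 2 × 9 × 1.5 = 27 of 114, or 23.7%.

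**2. Best guess.** Always guess the group with more places left. The expected success at places 1 to 6 is 0.5, 0.6, 0.6, 0.7, 0.7 and 1.0. The sum is 4.1, and 4.1/6 = 68%, against 50% by chance.

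**3. Film order.** 6/4 = 1.5, so equal cells within a block are impossible. Equality on each factor separately (3:3 and 3:3) is possible. The number of nap participants with a given order in a block is then 0, 1, 2 or 3 with probability 0.05, 0.45, 0.45, 0.05: never an even split, with variance 0.45. Over 19 blocks the SD is √(19 × 0.45) = 2.92 around 28.5 (95% range 23 to 34 of 57). The wake group mirrors the nap group, so the difference in proportions has SD 2 × 2.92/57 = 10 percentage points. Randomising order with no blocking would give √(2 × 0.25/57) = 9 points.

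**4. Alternatives.** At a fixed length the certain share is 33.3% for blocks of 4 and 20.0% for blocks of 8, so changing to a single multiple of four is not enough. With lengths 4 and 8 mixed at random, simulation with 57 per sex and an observer who knows the two lengths but not their sequence gives about 7% certain when only groups are tallied (4,000 runs). When film order is tallied too, which helps to reveal the block ends, it gives about 10% (1,500 runs). The best guess is right about 68% of the time in both cases.

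**The case against.** The strongest reply is that 25% is only what could be known. It requires knowing the block length and block starts and keeping a tally within each sex. The protocol does not say that session staff had the layout, and someone outside the sessions made the list. That stands, and a reader should not infer that staff did know a quarter of allocations. But the length is in print during recruitment and rows are uncovered in turn, so the risk is plausible.

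It can also be said that the decisions before allocation are mostly rule-based: five adherent nights, adherence on the two nights before testing, and a 30-minute limit on day 0. This largely stands. The discretion lies mainly in adjusting the schedule and agreeing to reschedule. The text attributes monitoring to the researchers in general and does not say that the person who uncovers rows takes these decisions.

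On film order, the sentence can be read as equality on each factor, which blocks of six achieve. A reader might infer that the scheme is impossible, or that the protocol breaks a promise of balance between nap and wake. It makes no such promise, and group balance stays 3:3. The imbalance is chance variation, about what unblocked assignment of order would give.

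A reader might also add the exclusion for watching less than 80% of the film. That does not belong here. By then allocation may already be open, and block lengths would change nothing.

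**Conclusion.** The point holds as a correctable weakness in concealment. One published block length within sex, with rows uncovered in turn, leaves 23.7 to 25% of group allocations open to certain prediction and a best guess right 68% of the time. The assumptions are 3:3 blocks, an observer who knows the length and starts, and a tally by sex. Cell blackout alone therefore does not secure the stated blinding up to the end of set-up. The protocol does not show that prediction or bias occurred, and no effect on the nap-wake estimate can be derived from it.

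Film order is secondary: blocks of six balance it overall but not within group, with an SD of about 10 percentage points for the nap-wake difference and probably little effect on the result.

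Timing also needs reconciling. Study design places assignment after the film, while Randomization lifts the researchers' blinding after set-up, which comes before the film.

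**What to change.** For participants still to be randomised, the independent list-holder generates a new list over the four cells (nap or wake by film order) within sex, with block lengths of 4 and 8 varied at random and not disclosed to session staff. The Randomization section is corrected to say what is balanced and from which date the new list applies, and it is reconciled with Study design on whether allocation is opened before or after the film.

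The cost is one list and a short text change. One block of six per sex may be left incomplete at the switch, an imbalance of at most three per stratum. The final block may also stop short, by at most four in a block of eight; the present scheme already has this feature, since 57 is not a multiple of six. A total of 114 cannot be equal over four cells (28.5 each), so near-equality is the aim.

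The change has two limits. It does nothing for those already randomised. It also removes most of the certainty but not the advantage of guessing the group that is behind, so schedule adjustment and rescheduling are best agreed by someone who has not seen the opened rows, if staffing allows.

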#### Recruitment and inclusion criteria

Participants are from a healthy population, aged between 18 and 49 years. Participants are recruited through advertisements on the Monash University Clayton and Caulfield campuses and word-of-mouth. The study is also advertised through social media.

Participants are screened to determine if they meet eligibility criteria via a phone call and online screening questionnaire. Table 1 outlines exclusion criteria. Table 2 outlines self-report questionnaires used as part of the screening process and further self-report questionnaires administered during the study. Informed consent is obtained following the phone call and prior to completing the screening questionnaire.

**Table 1 TB1:** Exclusion Criteria

Category	**Exclusion criteria**
*Psychological and neurodevelopmental disorders*	Current psychiatric conditions: bipolar disorder, psychosis, schizophrenia, depression, panic disorder or OCD, all personality disorders, substance use disorder
	Lifetime diagnosis of PTSD
	Score of 31 and above on the PCL-5 (assessment of current PTSD symptoms) for any Criterion A traumatic event
	Taking anti-depressant or anxiety medication
	Diagnosis of ADHD and/or taking stimulant medication
*Sleep*	Current sleep disorders
	Having a habitual sleep window that falls outside of a 22:00–01:00 bedtime and 06:00–09:00 wake time
	Taking sleep medication
*Neurological conditions*	All neurological conditions (including epilepsy), history of stroke, or acquired brain injury (except for mild concussions involving loss of consciousness <15 min)
	Experiencing frequent migraines, have experienced a migraine in the past 3 months or if migraines are triggered by mild sleep deprivation and/or flashing lights
*Language*	Not fluent in English
	Speaks French (Conversational level). One of the films involves dialogue in the French language. No subtitles are included
*Other*	Color blindness and/or any visual impairment/uncorrected visual acuity
	Experiencing hearing difficulties or ear pain
	Report having watched either of the films

**Table 2 TB2:** Self-Report Measures by Timepoint

**Self-report measures by timepoint**	**Description**
*Initial screening questionnaire*	
Epworth Sleepiness Scale [42]	8-item questionnaire measuring daytime sleepiness, cutoff score > 10.
STOP-BANG Questionnaire [43]	8-item questionnaire screening for Obstructive Sleep Apnea. Cutoff score > 3. Participants with scores above cutoff for both the Epworth Sleepiness Scale and STOP-BANG are excluded due to OSA risk.
Pittsburgh Sleep Quality Index (PSQI) [44]	19-item questionnaire which assesses sleep quality and disturbances over the previous month. Cutoff score > 5.
Alcohol Use Disorders Identification Test (AUDIT) [45]	10-item screening tool to assess alcohol consumption, drinking behaviors, and alcohol-related problems. Hazardous use cutoff defined as 10 or above.
Drug Use Disorders Identification Test (DUDIT) [46]	11-item self-administered screening instrument for drug-related problems. Cutoff >2 for females and >6 for males.
Patient Health Questionnaire (PHQ-9) [47]	Measure of depression severity, cutoff score of 10 (moderate depressive symptoms).
Generalized Anxiety Disorder Assessment (GAD-7) [48]	Measure for symptoms of anxiety, cutoff score of 10 (moderate anxiety symptoms).
PTSD Checklist for DSM-5 (PCL-5) [49]	20-item self-report measure that assesses the symptoms of PTSD according to DSM-5. Cutoff score of 31 and above for any Criterion A traumatic event endorsed in Life Events Checklist.
Life Events Checklist for DSM-5 (LEC-5) [50]	Assesses exposure to 17 events known to potentially result in PTSD or distress and includes one additional item assessing any other extraordinarily stressful event not captured in the first 16 items.
Health Questionnaire (females only)	This will ask participants about their menstrual cycle and will be conducted during the consent meeting.
*7 days at-home sleep monitoring*	
Sleep diary	Daily questionnaire asking about nighttime sleep, naps, alcohol and caffeine intake, medication, and flu symptoms. A separate version for those who menstruate queries menstrual cycle.
*Lab session*	
Mind Wandering Questionnaire (MWQ) [51]	5-item scale measuring the frequency of mind wandering.
Mindful Attention Awareness Scale (MAAS) [52]	15-item scale designed to assess a core characteristic of mindfulness.
Maladaptive Daydreaming Scale (MDS) [53]	16-item questionnaire designed to assess maladaptive daydreaming.
Perseverative Thinking Questionnaire (PTQ) [54]	15-item questionnaire assessing repetitive negative thinking (non-disorder specific).
Leuven Obsessional Intrusions Inventory (LOII) [55]	50-item self-report instrument designed to measure the frequency of intrusive thoughts, images, impulses, and doubts.
*Post-lab session: At-home cognitive testing and sleep monitoring*	
Sleep diary	Same as above.
Intrusive memory diary [13]	Diary of intrusive memories. Participants complete at least once per day following the lab session. 6 questions about timing, type, and content of intrusive memories, including level of distress.

### Ethics approval

This project has been approved by the Monash Human Research Ethics Committee (project number 40198) and is conducted at the Monash University Sleep and Circadian Medicine Laboratory, Melbourne, Australia.

During the initial phone call following expression of interest, participants are provided with extensive details about the study. Following this, if participants are interested, they are sent the consent form. The consent form includes information about research procedures, potential risks, reimbursement, confidentiality, and freedom to withdraw from participation. Participants also consent to data being used for future projects. Once the consent form is returned, participants are sent the screening criteria link.

A post-participation debrief meeting is held with each participant to identify any ongoing intrusive memories or distress. All debrief meetings are conducted by the project coordinator ([name]), who is a clinical psychologist. If necessary, resources are provided to participants for community-based services. Following completion of all study components, participants are reimbursed $200 AUD, prorated if the participant discontinues early.

### Procedure and materials

At-home sleep monitoring. For the duration of the experiment, participants wear actigraphy (GENEActiv, Activinsights Ltd., wrist-worn device) and complete daily sleep diaries. For the first eight nights, participants follow a regular sleep schedule, although they wake 2 h early on the day of the lab session. Participant sleep schedules, wake time on day 0 and the timing of the lab session are determined during an initial meeting (day −7 or the previous day) and is based on their regular sleep schedule. Adherence is documented via the sleep diaries and actigraphy.

#### Lab session (day 0)

##### Questionnaires

Five self-report questionnaires assessing spontaneous cognition are completed during polysomnography set-up at the beginning of the lab session. These include mind wandering, mindful attention, maladaptive daydreaming, perseverative thinking, and obsessional intrusions. Each measure is described in Table 2.

##### Polysomnography

Polysomnography recordings for each 2-h sleep or wake opportunity include a 6-channel electroencephalogram (EEG) montage, using electrodes F3/F4, C3/C4, and O1/O2. Eye movement is monitored through electrooculogram and chin activity through electromyogram. Electrical activity of the heart is also measured via electrocardiogram. To screen for obstructive sleep apnea and periodic limb movement disorder, measurement of pulse oximetry and limb movement is included. Participants assigned to the wake group are also monitored with polysomnography throughout the controlled wake period, except for pulse oximetry. Polysomnography recordings are not scored but are monitored throughout the 2-h wake opportunity. Researchers interact with the participant at the first sign of excessive sleepiness, including: (a) no longer engaging in activities provided; (b) closed eyes with reduced alpha, or (c) presence of low amplitude, mixed-frequency activity.

Primary sleep variables for the lab session nap include total sleep time, REM sleep percent, and duration. Examining REM is based on findings linking REM prior to [56] and post-experimental trauma exposure [26] with fewer intrusive memories and reduced distress associated with intrusions, respectively. Secondary sleep outcomes include slow wave sleep (SWS)% and duration. We will also explore the influence of microstructural alterations to frequency-specific EEG activity (eg, slow wave activity and theta and beta frequency during REM and NREM) during the nap on intrusion frequency and recognition memory task performance using quantitative spectral analysis of EEG. Spectral power analysis of EEG data is based on a previous study which found REM theta predicted fewer re-experiencing symptoms post trauma film exposure [24]. Exploratory analysis may include examining nap fragmentation and spindle analysis of NREM stage 2 sleep based on previous findings implicating higher spindle density in fewer reported intrusions [16].

